### Intervention

Every participant will receive a menstrual diary to monitor menstrual cycles. As recommended by the Australian evidence-based PCOS guidelines and International evidence-based PCOS guidelines, all women will receive evidence-based behaviour change coaching [9, 10] based on social cognitive theory and the behaviour change wheel [33]. This will involve a 2-h session including goal setting and goal striving, education regarding the importance of physical activity and healthy eating and education on effectively using media and resources for healthy eating and diet [34].

### Exercise interventions

Exercise will be conducted on stationary bikes in an individual setting. Exercise intensities will be prescribed and monitored using heart rates (percentage of heart rate reserve [HRR]), as described in Table 1. Sessions will be conducted at Victoria University fitness centres/exercise clinics under the supervision of accredited exercise physiologists [4, 12, 35–39]. Adherence and compliance will be determined from supervised exercise session attendance and completion of prescribed exercise (duration and intensity [percentage HRR]), respectively. Data from participants with less than 75% adherence will be included in the intention to treat analysis only. Any musculoskeletal injuries or changes in health status will be recorded via a provided web-based diary.

#### Volume matching and training progression

The SSE and HIIT intervention arms will be matched for training volume (metabolic equivalent task (MET).min/week) and progressed weekly by manipulating session duration and intensity. Both SSE and HIIT will progress from 312 MET.min/week in week 1 to 530 MET.min/week in weeks 6–12, meeting exercise guidelines [40]. Exercise sessions will include warm-up and cool down protocols, and will be adjusted weekly to individual capabilities and training adaptations [4, 41]. See Table 1 for details.

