### Randomisation and blinding

Following baseline testing, participants will be randomised to one of three 12-week interventions; HIIT, SSE or Con (details of the three treatment arms in Table 1). An independent biostatistician will randomise subjects by a simple randomisation procedure using computerised sequence generation with an allocation ratio of 1:1:1. Two tables based on BMI (< 35 kg.m^2^ or > 35 kg.m^2^) will be created. As exercise interventions cannot be blinded from participants and staff (accredited exercise physiologists) implementing the intervention, only staff undertaking sample analysis and endpoint data processing will be blinded to group allocation.

**Table 1 Tab1:** Details of the three treatment arms

Intervention	Details
Con	Standard care consisting of basic exercise advice (150 min/week) with no supervised or structured exercise. We do not anticipate the control group will engage in a significant amount of exercise compared to their baseline physical activity levels without the addition of a structured exercise program [11]
SSE group	Minimum physical activity recommendations (150 min per week) [40], in three supervised 50-min sessions/week of continuous moderate intensity exercise sessions of cycling at 50–60% HRR (~ 3.5 METs)
HIIT group	Minimum vigorous physical activity recommendations (~ 75 min per week) [40], in three supervised sessions/week of HIIT exercise (cycling/running). Based on existing literature, pilot data [43] and patient consultation, we will use a practical weekly training program encompassing two successful HIIT protocols [16, 17, 55]: two sessions/week of short constant load cycling of 12 × 1 min at > 85% HRR (> 9 METs; [1 min HIIT]) with 1 min active recovery; one session/week of cycling 6–8 × 4 min at > 85% HRR (> 9 METS; [4 min HIIT]) with 2 min active recovery

*Con* control- standard care, *SSE* supervised standard exercise, *HIIT* high-intensity intermittent training, *min* minutes, *MET* metabolic equivalent task, *HRR* heart rate reserve

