#### Preventing and managing injury

Absolute risk of cardiovascular disease in this young female population is low. However, participants will be screened with appropriate clinical monitoring during all exercise testing (ECG) and training sessions (heart rate and blood pressure monitoring) with individualised training prescription and progression reducing the risks of injuries and adverse events [4, 12, 35, 36].

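### SSE and HIIT are said to be volume-matched at 530 MET.min/week, but they are prescribed by % HRR, and Table 1's MET labels for the two bands do not agree, so matched volume need not result

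*Protocol article*

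**What the plan says.** Under Volume matching and training progression, the protocol article states that "The SSE and HIIT intervention arms will be matched for training volume", measured in MET.min/week. Both arms rise from 312 in week 1 to 530 in weeks 6-12, and the programmes are "progressed weekly by manipulating session duration and intensity". The same paragraph adds that "Exercise sessions will include warm-up and cool down protocols" and that sessions are adjusted each week to the individual.

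The operative prescription is in other units. Under Exercise interventions, "Exercise intensities will be prescribed and monitored using heart rates", as a percentage of HRR, and compliance is judged by "completion of prescribed exercise (duration and intensity [percentage HRR".

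Table 1 (under Randomisation and blinding) is the only place that links the two:
- **SSE:** three 50-minute sessions a week of "continuous moderate intensity exercise sessions of cycling at 50–60% HRR", labelled about 3.5 METs.
- **HIIT:** "two sessions/week of short constant load cycling of" twelve 1-minute bouts with 1-minute active recoveries, plus one session of six to eight 4-minute bouts with 2-minute active recoveries. All bouts are above 85% HRR and labelled above 9 METs.

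**The concern.** The match is stated in METs, but women train to heart rate and minutes. If the MET figures attached to the two heart-rate bands do not fit together, a woman can comply fully with her programme while the two arms accumulate different MET.min.

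This bears on what HIIT versus SSE can show. The Abstract and Discussion say the trial will give insight into the best exercise intensity, and the Discussion names the lack of volume-matched comparisons as the evidence gap. If achieved volumes differ, HIIT versus SSE mixes intensity with volume. If SSE does more and volume helps, a HIIT advantage would be conservative and a null result would be hard to read. If HIIT does more, part of any HIIT advantage could be due to volume.

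**Working it through.** **Inputs from Table 1.** SSE: 3 × 50 = 150 min/week. HIIT with k long bouts: work 2 × 12 × 1 + 4k = 24 + 4k min; recovery 24 + 2k min, counting one recovery per bout. So k = 6 gives 48 min work and 36 min recovery; k = 8 gives 56 and 40.

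**Step 1: reproduce 530 from the labels.**
- SSE: 150 × 3.5 = 525.
- HIIT, k = 6: work 48 × 9 = 432. Reaching 530 needs recovery at (530 − 432)/36 = 2.72 METs, which is plausible.
- HIIT, k = 8: work 56 × 9 = 504. Recovery at 2 METs adds 80, giving 584.
- Nominal ratio SSE/HIIT at k = 6: 525/530 = 0.99.

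The stated figure is therefore reachable on the labels, with warm-up and cool-down left out.

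**Step 2: test whether the labels agree.** Assumption (not in the article): % HRR equals either % of MET reserve with rest at 1 MET, or % of peak METs. P is peak METs.

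| Rule | P from SSE label (50-60%) | P from HIIT label (85-100%) |
|---|---|---|
| Reserve | 1 + 2.5/0.60 = 5.2 to 1 + 2.5/0.50 = 6.0 | 1 + 8/1.00 = 9.0 to 1 + 8/0.85 = 10.4 |
| % of peak | 3.5/0.60 = 5.8 to 3.5/0.50 = 7.0 | 9/1.00 = 9.0 to 9/0.85 = 10.6 |

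Put as ratios, the labels need at least 9/3.5 = 2.57 (net of rest, 8/2.5 = 3.2), while the heart-rate bands give at most 100/50 = 2.0.

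Exact linearity is not essential. For both labels to hold, heart rate would have to climb 50/2.5 = 20 to 60/2.5 = 24 points of % HRR per MET up to 3.5 METs. It would then climb only (85 − 60)/5.5 = 4.5 to (100 − 50)/5.5 = 9.1 points per MET up to 9 METs.

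**Step 3: volumes for one woman in either programme** (reserve rule, k = 6, recovery 2.72 METs, no warm-up counted).
- Fitness as the SSE label implies: SSE 525. HIIT from 48 × 4.54 + 98 = 316 (P = 5.2, 85%) to 48 × 6.0 + 98 = 386 (P = 6.0, 100%).
- Fitness as the HIIT label implies: HIIT 530. SSE from 150 × 5.0 = 750 (P = 9.0, 50%) to 150 × 6.65 = 997 (P = 10.4, 60%).

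**Step 4: how far this depends on unstated facts.** Let S and H be the METs at the SSE and HIIT intensities, and r the recovery METs. Then SSE = 150S and HIIT = (24 + 4k)H + (24 + 2k)r. Warm-up plus cool-down is assumed to be 10 min/session at 3 METs, or 90 MET.min/week. Outside the 50 minutes, it adds 90 to both arms. Inside, SSE becomes 120S + 90 and HIIT gains 90.

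Grid: P = 6 to 11 in steps of 1; SSE 50, 55, 60%; HIIT 85, 90, 95, 100%; k = 6, 7, 8; r = 2, 3, 4. That is 648 combinations per rule, 1296 for both rules, and 3888 over three warm-up treatments.

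| Warm-up and cool-down | SSE/HIIT ratio | Below 1 | Within 0.90-1.10 |
|---|---|---|---|
| Not counted | 0.91-1.99 | 9 of 1296 | 53 of 1296 |
| Outside the 50 min | 0.92-1.84 | 9 of 1296 | 64 of 1296 |
| Inside the 50 min | 0.77-1.50 | 262 of 1296 | 593 of 1296 |

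Overall 280 of 3888 fall below 1. These are counts of assumed scenarios, not probabilities.

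**The case against.** **The labels are approximate.** Table 1 marks them as about 3.5 and above 9, which may be broad intensity classes and not each woman's oxygen cost. That is fair as to their purpose, but approximation does not close a gap between a peak of at most 7 METs and one of at least 9, and a value above 9 widens it. The linear rules are indeed weakest for 1-minute bouts, which make up 24 of the 48-56 weekly work minutes, so the HIIT volumes in the working are soft.

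**530 is not wrong.** This stands. It follows from the labels at six long bouts. The excess at eight takes the top of a stated range and does not show an arithmetic error.

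**Individual adjustment could restore the match.** Progression uses both duration and intensity, and the section on injury describes "training sessions (heart rate and blood pressure monitoring) with individualised training prescription". Graded tests with gas analysis exist, so individual METs could be used. The full protocol may contain such a rule, and an article need not print it. This stands to the extent that one can say only that a match need not result. Adjustment that relied on the printed labels would carry their conflict forward.

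**A reader might infer that SSE certainly receives more volume.** The documents do not support that. SSE is mostly higher when it keeps a full 150 minutes of work. If warm-up and cool-down fall inside the 50 minutes, which is a natural reading of the text, 593 of 1296 combinations (46%) lie within 10% of equality and 262 (20%) favour HIIT.

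**Conclusion.** The point holds in a limited form. The matching claim is stated in MET.min, the prescription and compliance check are in % HRR and minutes, and the labels joining them cannot both be right for women of the same fitness if % HRR tracks METs or MET reserve even roughly linearly. Randomised arms should be of similar fitness, so different women in each arm do not resolve it. Training to the stated % HRR and minutes therefore need not give matched volume.

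The document does not determine the size or direction of any mismatch. The ratio range of 0.77 to 1.99 rests on assumed peak capacity, recovery intensity and warm-up treatment. A reader might also infer that the trial's main comparison is compromised. It is not: the hypothesis and planned contrast compare the arms and do not depend on equal volume. The randomised comparison of programmes as delivered, HIIT versus Con and the primary analysis are unaffected. This is a minor point on how HIIT versus SSE may be described.

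**What to change.** 1. Correct Table 1's MET labels so that they agree with the % HRR bands, for example from the baseline graded-test heart rate and oxygen-uptake data.
2. Estimate achieved MET.min/week by arm for weeks 6-12 from whatever session heart rate and duration records are kept for compliance. Present it as approximate, especially for the 1-minute bouts.
3. Set an agreement margin before the data are seen. Call HIIT versus SSE volume-matched only if achieved volumes agree within it; otherwise describe it as a comparison of two programmes as delivered.

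The cost is a wording correction and one descriptive analysis, with no change to randomisation, visits or the primary analysis. Two limits apply. The article says heart rate is monitored, not that continuous traces are stored, so separating work from recovery in short bouts may not be possible. Graded tests are done only before and after the intervention, so values for weeks 6-12 would need interpolation. The downside is that the volume-matched claim may have to be softened.

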#### Preventing and managing injury

Absolute risk of cardiovascular disease in this young female population is low. However, participants will be screened with appropriate clinical monitoring during all exercise testing (ECG) and training sessions (heart rate and blood pressure monitoring) with individualised training prescription and progression reducing the risks of injuries and adverse events [4, 12, 35, 36].

### Post-intervention assessment

Within 4 days after the final exercise session (HIIT or SSE) or following 12 weeks (Con) the hyperinsulinemic-euglycemic clamp, questionnaires (SF-36, PCOSQ, IPAQ and DASS-21), muscle and fat biopsies, body composition measures (DXA, weight, waist and hip circumferences) and graded exercise tests will be repeated. Women will be asked to abstain from training or physical exercise during this period. An accelerometer will be given (or mailed if in the control group) 7 days before post-intervention testing to assess exercise in this period. They will again be asked to complete a 3-day food dairy.

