### Outcome measurements

Outcome measures will be taken pre-intervention and post-intervention (Fig. 1). The primary outcome is the change in insulin sensitivity (measured by the steady state glucose infusion rate determined during the hyperinsulinemic-euglycemic clamp) between the three interventions. Secondary outcomes include reproductive health via hormone profiles (AMH and steroid profiles), mental health and health-related quality of life, body composition, physical activity behaviours and cardio-respiratory fitness.

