### Statistical methods and determination of sample size

Primary analyses will be undertaken on an intention-to-treat basis, including all participants as randomised, regardless of treatment actually received. The HIIT group will be compared with the SSE and Con groups using a planned contrast of change from baseline to the week 12 endpoint on the basis of insulin sensitivity scores using a mixed-model repeated measures analysis. Stratification variables will be evaluated and retained in analyses where they are measured as significant or quasi-significant. Transformation of scores, including categorisation, may be undertaken to meet distributional assumptions and accommodate outliers. Comparisons of changes in insulin sensitivity scores from baseline to other time points will be undertaken as secondary analyses. Data will be analysed by SPSS and significance will be accepted when *p* < 0.05. Where required *p* values from the statistical analysis will be adjusted for multiple comparisons using the false discovery rate [49] and statistical significance will be accepted when false discovery rate q < 0.1.

Using the primary outcome of change in insulin sensitivity (as measured by the glucose infusion rate) of 27 mg/min/m^2^ (effect size (Cohens d) = 0.25) in response to training [4], we require a total of 42 participants or *n* = 14 per group to achieve a power of 85% (α = 0.05). With an approximate attrition rate of 30% based on previous research, we will recruit 60 participants [4, 12].

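### The only scheduled post-baseline clamp is timed by the final exercise session in HIIT and SSE but by 12 weeks in Con, so an exerciser who stops early gets either an off-time value or no test date

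*Protocol article*

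**What the plan says.** All references are to the protocol article.

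- **Post-intervention assessment** gives the timing rule: "Within 4 days after the final exercise session (HIIT or SSE) or following 12 weeks (Con"). The tests it governs include "the hyperinsulinemic-euglycemic clamp, questionnaires (SF-36, PCOSQ, IPAQ and DASS-21), muscle and fat biopsies", together with body composition and the graded exercise tests. The same paragraph has an accelerometer issued 7 days before this testing.
- **Outcome measurements** defines the primary outcome as change in insulin sensitivity, "measured by the steady state glucose infusion rate determined during the hyperinsulinemic-euglycemic clamp", with measures taken before and after the intervention.
- **Statistical methods and determination of sample size** states: "Primary analyses will be undertaken on an intention-to-treat basis, including all participants as randomised, regardless of treatment actually received". The primary comparison is a "planned contrast of change from baseline to the week 12 endpoint".
- **Exercise interventions** adds: "Data from participants with less than 75% adherence will be included in the intention to treat analysis only".
- **Follow-up**, at 6 and 12 months, lists questionnaires only.
- The sample size paragraph states: "With an approximate attrition rate of 30% based on previous research, we will recruit 60 participants".

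**The concern.** The primary estimate needs a week-12 clamp value from every randomised woman, however much she trained. The scheduling rule supplies that value by the calendar in Con, but through an exercise event in HIIT and SSE. An event that depends on adherence is a poor trigger for an intention-to-treat endpoint. Among women who stop training, the clamp may be taken early or may have no date at all, and this can happen in two arms only.

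The analysis could then drift towards a comparison of women who completed training, or mix early and week-12 values in the exercise arms. If women who stop gain less by week 12 than those who continue, either outcome flatters exercise against Con. The document schedules only one clamp after baseline. The statistical section mentions secondary comparisons of insulin sensitivity at other time points, but no visit that would supply them is described. A mixed model would have no intermediate clamp to draw on for a woman whose single value is missing.

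**Working it through.** **Step 1. Apply the stated rule to each kind of participant.**

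| Participant | Clamp under the stated rule | Week-12 value? |
|---|---|---|
| Con, any behaviour | following 12 weeks | yes |
| HIIT or SSE, trains to the end of week 12 (with or without missed sessions) | within 4 days of the last session | yes |
| HIIT or SSE, stops early; rule read as her actual last session | within 4 days of stopping | no, off time |
| HIIT or SSE, stops early; rule read as the scheduled last session | she has no such session | no date stated |

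Under either reading, the early stopper in an exercise arm is the only case for which the rule fails to deliver what the primary analysis calls for.

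**Step 2. Which reading is more natural?** The accelerometer goes out 7 days before testing, and testing is at most 4 days after the final session. It must therefore be issued at least 7 − 4 = 3 days before that session. That is possible only if the last session is known in advance. The rule thus fits women who finish the 12-week programme and was probably written for them.

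**Step 3. Timing drift if the rule is read as the actual last session (assumed inputs).** Suppose a share s of an exercise arm stops at week w and is tested then. The arm's mean test time is 12(1 − s) + ws.
- s = 0.10, w = 9: 10.8 + 0.9 = 11.7 weeks.
- s = 0.30, w = 3: 8.4 + 0.9 = 9.3 weeks.

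Con stays at 12.

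**Step 4. Possible effect on exercise versus Con (illustration).** The 27 mg/min/m² is the protocol's planning change. Everything else is assumed: completers gain 27, Con does not change, a share s stops, and stoppers retain a fraction k of the gain at week 12. The week-12 effect in all randomised women is 27[(1 − s) + sk].
- s = 0.30, k = 0: 0.7 × 27 = 18.9. Completers only shows 27; 27/18.9 = 1.43, or 43% too large.
- s = 0.30, k = 0.5: 18.9 + 0.3 × 13.5 = 22.95; 27/22.95 = 1.18, or 18% too large.
- s = 0.30, k = 0, stoppers tested at week 4 with one third of the gain (9): 18.9 + 0.3 × 9 = 21.6; 21.6/18.9 = 1.14, or 14% too large.
- s = 0.10, k = 0: 0.9 × 27 = 24.3; 27/24.3 = 1.11, or 11% too large.
- k = 1: no overstatement at any s.

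**Step 5. HIIT versus SSE.** Both arms share the anchor, so equal stopping creates no difference where none exists. Unequal stopping can hide or create one. With 27 in completers of both arms, k = 0, and stopping of 10% in one arm and 30% in the other, the week-12 difference is 24.3 − 18.9 = 5.4. Completers only shows 0.

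**Step 6. What the 30% is.** 42/(1 − 0.30) = 60 reproduces the recruitment target. The 30% is an allowance for overall study attrition, Con included. The document does not say that it measures stopping training.

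**The case against.** The strongest reply is that the final exercise session plainly means the last one scheduled. The programme is fixed at 12 weeks, the accelerometer step needs a known test date, and Con is worded differently only because it has no sessions. On this view the anchors agree, and what remains is a missing visit rule for women who discontinue, which a condensed article may leave to the full protocol.

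The first part stands: this is the more natural reading, and completers are tested on time. The second does not fully answer the point. The article does state a trigger for the primary clamp. That trigger cannot be met by an exerciser who has stopped, while the same article requires her week-12 value. This is a conflict between stated rules, not only absent detail.

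Several stronger inferences are not supported:
- A reader might conclude that women who stop are never tested. No section says so, and the sentence on adherence below 75% implies that such women are meant to have data.
- A reader might suppose that made-up sessions push the clamp past week 12. No make-up rule is given.
- A reader might apply the 30% to the 40 exercisers and count 12 affected women. That treats study attrition as stopping training. Women who withdraw from the study altogether would not be recovered by any change of anchor.

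**Conclusion.** The point holds in a limited form. The stated trigger for the primary clamp works for Con and for exercisers who train to week 12. It fails for exercisers who stop early: depending on the reading, their value is off time or has no date. Timing or missingness of the primary endpoint can therefore depend on adherence in HIIT and SSE alone. That may bias exercise versus Con, and HIIT versus SSE if stopping differs between them.

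The size of the bias cannot be determined from the document. The 14% to 43% range shows only what could happen with a 30% stopping share, no change in Con and the assumed stopper gains. It is smaller with fewer stoppers, and nil if stoppers keep the full gain. The direction is also conditional on stoppers gaining less. The wording should be corrected before the endpoint visits are run, because no later clamp is scheduled that could replace a missed one.

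**What to change.** Reconcile Post-intervention assessment, Exercise interventions and the statistical section as follows.

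1. Set the post-intervention assessment in all three arms at 12 weeks from randomisation, or from a start date defined the same way in every arm, with one common window.
2. State that women who stopped or missed training are still invited to the already planned tests at that time.
3. Record stopping training separately from withdrawing from assessment, so that the two can be reported by arm.
4. Have the investigators settle how the 4-day interval after exercise fits this rule for women still training at week 12.

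No test is added. The cost is protocol wording, a scheduling rule and the effort of recalling women who stopped training.
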